## Discussion

To our knowledge this is the first study to evaluate the impact of cultural change on racial inequities in care for patients with sepsis. Aligned with NIH and NIGMS priorities, the results of this study are expected to: 1) further the nascent scientific literature on conceptualizing and measuring structural racism and health outcomes, 2) generate community-driven innovations in sepsis care for dissemination through national organizations such as American College of Chest Physicians, and 3) provide much-needed evidence to inform local and national dialogue around structural racism and health. We fully recognize this study is an audacious proposition. It not only addresses a highly sensitive topic (structural racism), but it also seeks to make measurable change in the structural root causes of inequities in sepsis care. Importantly, we have balanced our ambitions for whole system change with careful operationalization of core constructs and detailed measurement approaches to understand the mechanisms of change. Further, the proposed study may be especially audacious in the context of COVID-19, which will likely strain organizational capacity to participate in change initiatives and is expected to change patient care processes and outcomes. As described above, a period of systematic stakeholder engagement will allow us to adapt the intervention for feasibility in the ever-changing context of COVID-19. Further, given the well-document impact of the pandemic in exposing structural racism and exacerbating racial inequities, the proposed study is both timely and urgent.

We have anticipated several potential limitations in the proposed methodology. First, to mitigate social desirability bias (participants reporting socially acceptable, rather than authentic, responses) [99], we will use established techniques including attention to our own positionality and engagement of a diverse research team, engagement of a wide range of key informants across the project, use of interview guides with scripted probes to elicit details that would be difficult to misrepresent, encouraging participants to share both positive and negative experiences, and cultivating longitudinal relationships to encourage candor [100–102]. Second, clinical outcomes data will be derived from the EHR, which is known to have high rates of missing or misclassification of socially assigned race. Although this is concerning, 1) evidence indicates that EHR-based clinical data provides more objective estimates than claims-based data for sepsis surveillance [4], 2) any bias is likely toward the null (as most errors are of identifying LatinX patients as NHW) [103–105] and 3) there is no alternative. Further, we anticipate that some sites may use this project as an opportunity to highlight and correct for historical underinvestment in systematic, reliable capture of socially assigned race and other important demographics in their EHR. Third, Coalition turnover is expected to occur, limiting paired analyses of quantitative data. However, our prior research found that neither coalition size nor turnover was associated with intervention outcomes [30] (an association that we will evaluate in the proposed study as well). Further, organizations that were more successful in driving changes in organizational culture were observed to proactively adjust their coalition membership to adapt to changes in organizational leadership, to engage emerging champions, and to account for the specific aspects of AMI care they were addressing. Additionally, our study is designed to measure systems-level (rather than individual-level) phenomena, and we anticipate that the roles represented on the coalitions will remain relatively stable even as individuals come and go. Fourth, as with all health interventions there is a lag in time between implementation of practice change and corresponding adjustments in outcome rates. Subsequently, we plan to track difference in AA/B and NHW patients and LatinX and NHW patients for each of our clinical outcomes for 2.5 years post intervention implementing different lag periods (up to 6 months of lag time between the end of the intervention and time of observed clinical outcomes). Fifth, we may face limitations in attributing observed changes to the intervention. Hospitals will be exposed to multiple sources of knowledge during the intervention and may also undergo substantial internal shifts in staff and priorities. The mixed methods design of the proposed study is expected to allow us to capture and understand factors beyond the intervention that may be influencing the results.

This project is expected to provide a solid foundation for natural extensions of future work to address racial inequities in health outcomes nationally, including: 1) adapting the intervention to address other clinical conditions for which structural racism is a major influence such as diabetes and heart disease, 2) if the intervention is successful, conducting implementation science studies to determine the necessary dose and core components of the intervention to inform efforts to scale up nationally, and 3) sustaining and enhancing our productive partnership with MCCN to serve as a platform for investigation of basic science and clinical innovations in sepsis. Finally, because this is practice-informed scholarship, we anticipate that systems will generate novel strategies and tools for clinical management of sepsis. This was the case in LSL, where we received two grants to support knowledge translation and packaging of tools for AMI care generated by the study [106]. There is a substantial opportunity to partner for practical dissemination of results and associated ‘toolkits’ through national organizations such as CHEST, Sepsis Alliance, and the Society of Critical Care Medicine.

Addressing the impact of structural racism on sepsis care will require urgent and courageous action across health systems and community institutions, supported by ways of working to collaborate effectively across historical, political, and organizational boundaries. Aligned with calls to action by the NIH and Sepsis Alliance to address inequities in sepsis care and outcomes, this paper outlines an ambitious and rigorous interventional mixed methods approach. It is the first study to intervene prospectively to mitigate effects of structural racism by developing the domains of organizational culture that are required for anti-racist action. The results of this study are expected to have implications for providers, policymakers, and other healthcare professionals committed to addressing systemic racism within and beyond care for patients with sepsis.

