
#### Analytic approach

We will conduct a comparative interrupted times series (ITS) analysis to examine the relation between the intervention and racial/ethnic differences in sepsis clinical outcomes between AA/B and NHW patients and between LatinX and NHWs. The analysis will be performed separately for our three key outcomes: 1) time to antibiotics, 2) in-hospital mortality, and 30-day readmission and stratified by response to the intervention (change/no change) (Additional File 1; Supplemental Fig. 5). We will consider a pre-exposure to the intervention time beginning 2.5 years (10 quarters) prior to starting the intervention and a postexposure period comprising 2.5 years (10 quarters) following the start of the intervention, with estimates made at every calendar quarter. ITS will be utilized to determine the difference in quarterly rates over time between changers (systems that responded to the intervention) and non-changers, health systems that did not respond to the intervention. Subsequently, ITS allows us to detect if an intervention has impact above and beyond secular trends when randomization is not a feasible option, and is ideal for evaluation of data collected across multiple equally spread time points by testing the changes in the slope of an outcome over time [96]. Additionally, ITS requires at least eight observations pre and post intervention [97]. We will utilize generalized mixed effect models in conjunction with segmented regression to evaluate the effectiveness of our intervention [98]. The model will control for patient-level characteristics, including age, sex, insurance status, Charlson Comorbidity index, and admission through the Emergency Department or transfer from another acute care facility, and hospital-level characteristics including size, academic vs community hospital, number of intensive care beds, annual sepsis case volume. We will also account for seasonality based on calendar quarter by including a “season” term alone and interacted with the treatment indicator and will assess for any residual autocorrelation using autoregressive integrated moving average (ARIMA). To allow a marginal interpretation of results, we will use a linear probability model for all analyses. Because outcomes of patients within a hospital are expected to be correlated, we will account for these non-standard variance–covariance structures by clustering at the hospital level. All coefficients will be modeled as fixed effects.

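### The toward-the-null argument for race misclassification holds for a change in the LatinX–NHW gap only if miscoding is stable and unrelated to outcome, and the plan itself allows that capture may change

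*Protocol article*

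**What the plan says.** In the Discussion, the second limitation says clinical outcomes come from the EHR, "which is known to have high rates of missing or misclassification of socially assigned race". One of the reasons for accepting this is that "any bias is likely toward the null (as most errors are of identifying LatinX patients as NHW". The next sentence anticipates that "some sites may use this project as an opportunity to highlight and correct for historical underinvestment in systematic, reliable capture of socially assigned race".

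The Analytic approach section defines what is estimated. The series opens with "a pre-exposure to the intervention time beginning 2.5 years (10 quarters) prior to starting the intervention". It then runs for a further 10 quarters from the start. Interrupted time series (ITS) analysis is described as "testing the changes in the slope of an outcome over time", and the comparison is between groups of systems: "ITS will be utilized to determine the difference in quarterly rates over time between changers (systems that responded to the intervention) and non-changers". The listed adjustment terms are patient and hospital characteristics and season. None represents a change in how race is recorded.

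**The concern.** Attenuation is the right description of a gap measured under one fixed, random miscoding process. Aim 3 estimates something else: the movement of the gap across the start of the intervention, compared between changers and non-changers. If the miscoding rate itself moves after the start, the recorded gap moves even when care does not, and segmented regression cannot tell the two apart. The assurance about direction is then not available for this estimand. What is at stake is the LatinX–NHW result: a real reduction could be missed or could appear as a worsening, and the article would lead the reader to expect attenuation only.

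**Working it through.** The article attaches no figure to the misclassification statement, so there is none to reproduce.

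**Inputs.** From the article: the dominant error is LatinX recorded as NHW; there are 10 quarters before and 10 after the start; the meaningful difference in time to antibiotic is 30 minutes. Assumed, because the article gives none of them: the share *m* of LatinX patients recorded as NHW, the true LatinX:NHW patient ratio *r*, and the size of the gap.

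**Formula, non-differential error.** The recorded LatinX group loses members but keeps its mean. The recorded NHW group contains a fraction *mr*/(1 + *mr*) of LatinX patients. So

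recorded gap = true gap / (1 + *mr*).

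**Step 1: stable miscoding.** Take *r* = 0.5 and *m* = 0.4 throughout, with a true fall from 30 to 15 minutes. The recorded gap goes from 30/1.2 = 25.0 to 15/1.2 = 12.5, an observed fall of 12.5 against a true 15. Toward the null is correct here.

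**Step 2: capture fully corrected, no true change, assumed 5-point gap.** The apparent widening is 5 × *mr*/(1 + *mr*).

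| LatinX / NHW share | *m* = 10% | *m* = 40% |
|---|---|---|
| 10% / 70% | 5 × 1/71 = 0.07 | 5 × 4/74 = 0.27 |
| 25% / 55% | 5 × 2.5/57.5 = 0.22 | 5 × 10/65 = 0.77 |

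The gap therefore appears to grow by about 0.1 to 0.8 points with no change in care.

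**Step 3: the same on a 30-minute gap, *m* falling to 5%.**

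| *r* | *m* before | No true change | True fall 30 to 27 |
|---|---|---|---|
| 0.2 | 30% | 28.3 to 29.7 (+1.4) | 28.3 to 26.7 (−1.6) |
| 0.5 | 30% | 26.1 to 29.3 (+3.2) | 26.1 to 26.3 (+0.3) |
| 1.0 | 40% | 21.4 to 28.6 (+7.1) | 21.4 to 25.7 (+4.3) |

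A true 3-minute reduction is roughly halved, hidden or reversed, depending on *r* and *m*. With *r* from 0.1 to 0.2 and *m* from 20% to 40%, the artefact is only 0.4 to 1.9 minutes.

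**Step 4: what a false reduction requires.**
- *Differential error.* Suppose miscoded patients have no gap at all and correctly coded ones have 30 minutes. With *m* falling from 30% to 5%, the recorded gap goes from 30 to 0.70 × 30/0.95 = 22.1, a false fall of 7.9. If miscoded patients instead have 1.5 times the gap (*r* = 0.5), the recorded gap rises from 24.1 to 32.9. The direction depends on who is miscoded.
- *Uneven improvement.* With *r* = 0.5 and *m* falling from 30% to 5% in non-changers only, the contrast moves 3.2 minutes in the intervention's favour. In changers only, it moves 3.2 minutes against. If both groups improve alike, it largely cancels.
- *Missing race.* Assigning a race to patients who had none can move the gap either way; the article gives nothing to size it.

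**Step 5: the AA/B–NHW gap.** LatinX patients enter only through the NHW reference. With a true AA/B gap of 30, *r* = 0.5 and *m* falling from 30% to 5%, the recorded AA/B gap moves by +3.2 if the LatinX gap is also 30, by 0 if LatinX and NHW outcomes are equal, and by −1.6 if LatinX outcomes are 15 minutes better.

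**The case against.** The best defence has four parts.

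1. The article says only that sites may improve capture, so the problem may not arise. That stands as a limit on likelihood. The sentence on direction, however, carries no condition.
2. With non-differential error the artefact works against the intervention and is mostly small, so a positive finding would be safe from it within a site. That is largely right. But an error that can reverse the sign of a change is not attenuation, and a null or adverse LatinX result would be misread.
3. The fifth limitation already admits that internal changes may confound attribution, and the mixed-methods work may record them. That helps interpretation but does not adjust the estimates.
4. Date logs and recoding tables are detail that a condensed article leaves to the full plan. Their absence alone would be no finding; the finding is the stated inference.

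A reader might infer more: that better capture would manufacture a benefit, concentrated at changer sites and as large as the mortality threshold. The documents do not support this. On an assumed 5-point gap, correcting 20% to 40% of LatinX records gives a false fall of 1.0 to 2.0 points only if the miscoded patients have no disparity and correction is complete. On a 1-point gap the same arithmetic gives 0.2 to 0.4. The mortality threshold is a difference above 1%, so 1.0 does not exceed it. Sites are classed as changers on survey score or qualitative culture shift, not on data repair, so a link to that label is conjecture. Nor is the remark that no alternative exists clearly wrong: it follows a comparison of EHR with claims data and most naturally concerns the data source.

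**Conclusion.** The claim about direction of bias is too broad for the Aim 3 estimand. It is correct for stable, non-differential LatinX-to-NHW miscoding, and the next sentence of the same limitation raises the prospect that miscoding will not be stable. The best-supported consequence is an apparent widening of the LatinX–NHW gap that hides or reverses a true reduction: about 0.1 to 0.8 points on an assumed 5-point gap, or 0.4 to 7.1 minutes on 30 minutes over *r* from 0.1 to 1.0 and *m* from 20% to 40% falling to 5%. It is small where LatinX patients are few relative to NHW. A false reduction is possible only under the further conditions in Step 4, and its size cannot be set from the documents. All values of *m*, *r* and the gap are assumptions. This should be corrected, but it does not undermine the design.

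**What to change.** Limit the sentence in the second limitation to stable, non-differential LatinX–NHW miscoding, and say that improved capture during the study can move the recorded gap.

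Have each site prospectively log the date of any change in race/ethnicity capture, track completeness by site and quarter, and retain overwritten values. This has to start early, because overwritten values may not be recoverable.

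Keep the main ITS as planned and add two sensitivity analyses:
- (a) drop site-quarters after a capture change;
- (b) hold the recorded race definition constant in patients who have both values, with old against new coding tabulated.

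Do not back-fill only from later encounters, because patients who died cannot be corrected. A site-specific step at the capture date belongs only in sensitivity analysis, and only where that date is separable from the intervention start; otherwise the two steps are nearly collinear. A single constant coding process for all 20 quarters is not workable as the main analysis, since patients first registered after a change have no earlier value.

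The cost is a simple log, a little more analysis and less precision in the sensitivity analyses. Analysis (a) has a limit that should be stated: the article asks for at least eight observations after the start, so a site can lose only 10 − 8 = 2 post-start quarters before its own series falls short.

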## Data Availability

Not applicable—No datasets or materials have been generated or analyzed as part of this prospective description of the study protocol.

## Abbreviations

AA/B: African American/Black
AMI: Acute Myocardial Infarction
EHR: Electronic Health Record
ITS: Interrupted times series
LSL: Leadership Saves Lives
MCCN: Mayo Clinic Care Network
NHW: Non-Hispanic White
RSMR: Risk-Standardized Mortality Rate
